## Abstract

**Background:**

A common and potentially life-threatening complication of the treatment of childhood cancer is infection, which frequently presents as fever with neutropenia. The standard management of such episodes is the extensive use of intravenous antibiotics, and though it produces excellent survival rates of over 95%, it greatly inconveniences the three-fourths of patients who do not require such aggressive treatment. There have been a number of studies which have aimed to develop risk prediction models to stratify treatment. Individual participant data (IPD) meta-analysis in therapeutic studies has been developed to improve the precision and reliability of answers to questions of treatment effect and recently have been suggested to be used to answer questions regarding prognosis and diagnosis to gain greater power from the frequently small individual studies.

**Design:**

In the IPD protocol, we will collect and synthesise IPD from multiple studies and examine the outcomes of episodes of febrile neutropenia as a consequence of their treatment for malignant disease. We will develop and evaluate a risk stratification model using hierarchical regression models to stratify patients by their risk of experiencing adverse outcomes during an episode. We will also explore specific practical and methodological issues regarding adaptation of established techniques of IPD meta-analysis of interventions for use in synthesising evidence derived from IPD from multiple studies for use in predictive modelling contexts.

**Discussion:**

Our aim in using this model is to define a group of individuals at low risk for febrile neutropenia who might be treated with reduced intensity or duration of antibiotic therapy and so reduce the inconvenience and cost of these episodes, as well as to define a group of patients at very high risk of complications who could be subject to more intensive therapies. The project will also help develop methods of IPD predictive modelling for use in future studies of risk prediction.

## Background

Children undergoing treatment for malignancy have an excellent chance of survival, with overall rates approaching 75% [1]. In most cases, children who die following treatment for cancer do so as a result of their disease, but despite huge improvements in supportive care, around 16% of deaths within 5 years of diagnosis are due to the complications of therapy [2,3]. One such life-threatening complication in immunocompromised children remains infection, which frequently manifests as the occurrence of fever with neutropenia [4].

In adopting a policy of aggressive inpatient intravenous antibiotic use in such episodes, the mortality rate related to these episodes has improved dramatically (from 30% in the 1970s to 1% in the late 1990s) [4]. Intensive care management is required in less than 5% of cases [5-7], although a substantial proportion of children have complications which require specialised care [7]. There remain many episodes of febrile neutropenia (FNP), possibly two-thirds or more, among patients in whom no significant infection is identified and in whom this aggressive management strategy is likely to be excessive [7].

To better inform the clinical management of children with cancer and FNP, there is increasing interest in using risk prediction models (also known as 'prognostic models') and clinical decision rules (CDRs) [8-10]. Risk prediction models utilise multiple prognostic factors in combination to predict the risk of a future health outcome for an individual on the basis of their set of prognostic factor values. A CDR recommends a particular clinical action (or inaction) for an individual on the basis of the prediction (for example, the predicted probability, or 'risk score') derived from the model.

A robust risk prediction model which identifies those children at very low risk of having a significant infection could result in reduced intensity and/or duration of antibiotic therapy in the hospital. It could also form the basis of a randomised controlled trial (RCT) of alternative management approaches (for example, ambulatory oral antibiotics vs inpatient intravenous antibiotics) and would be the ideal way of informing the sample size required by reliably predicting the proportion of events expected in a low-risk group. This would lead to reduced costs for the healthcare system and the patient and family [11], as well as potentially a better quality of life for all affected. At present, there are many differing policies for the management of FNP in practice [12,13] but a lack of agreement about how and which CDRs, if any, are used.

Assessment of the risk of adverse outcome of each episode of FNP has been undertaken by many different groups, with many of them creating a CDR which aims to allow clinicians to accurately judge risk and treat patients appropriately. However, none of these analyses have resulted in a widely used risk stratification model, and current practice is variable, both in the United Kingdom [12] and internationally [13-15]. Some centres use a risk-stratified, reduced-intensity approach, and others treat all children aggressively. The essential problems with research in this area are common across much of paediatric practice: those of rare conditions with small numbers of cases and limited collaboration in primary studies. The modelling studies that have been done have incorporated different clinical features and outcomes and have used different methodologies, and it is therefore difficult to draw meaningful conclusions from this body of evidence. Calls for collaborative trials [16-18] have led to little progress.

This setting provides an ideal opportunity to undertake a collaborative, pooled analysis of the existing data sets in the form of an individual participant data (IPD) meta-analysis. In this effort, we will collect and reanalyse the original study data, which will permit reanalysis of the same clinical features across studies using a consistent approach and provide sufficient numbers to draw more robust and reliable conclusions. The findings of this work should therefore more robustly inform practice and future therapeutic RCTs. The analysis can be approached from three methodological directions: testing existing CDRs for their ability to 'diagnose' adverse outcomes, assessing the added value of individual prognostic factors and building a more accurate predictive rule containing a parsimonious set of prognostic factors.

### Systematic reviews of existing knowledge

In preparation for this project, two systematic reviews were undertaken to assess the prior knowledge of the discriminatory ability of CDRs [19] and inflammatory serum markers ([name], [name], [name], [name], [name]) in children and young people with FNP. The systematic review of CDRs initially identified 2,057 potential studies and finally included 24, of which 21 had data in a usable format. It showed that two groups of studies have been undertaken to risk-stratify children who present with FNP. Researchers in the first group of studies examined the use of clinical examinations to predict radiographic pneumonia (4 studies) [20], and investigators in the second group examined more general infectious complications (20 studies) [19].

Among the studies in which general infectious complications were examined, 16 separate models were produced and contained 9 data sets used to validate previously derived models. The researchers studied a variety of outcomes with individual differences in definitions, but covered five main categories: death, critical care requirement, serious medical complications, significant bacterial infections and bacteraemia.

Only one rule could reasonably be assessed across multiple data sets: that of absolute monocyte count and temperature criteria proposed by Rackoff *et al. *[21] to exclude bacteraemia. The most appropriate meta-analysis of the rule's effectiveness led to estimates of moderate discriminatory ability, with the average probability of bacteraemia in the groups being low risk = 6% (95% CrI = 1% to 34%), middle-level risk = 18% (CrI = 3% to 37%) and high risk = 49% (95% CrI = 6 to 84%).

Of the other rules, the model of Santolaya *et al. *[22] showed a good ability to differentiate between low- and high-risk groups when a wider definition of 'serious infection' was used, with average predictive ability estimated as low risk = 13% (95% CI = 9% to 18%) and high risk = 72% (95% CI = 68% to 75%). The rule has been developed and tested in Chile and may be of limited applicability in Western Europe and North America [23]. Other rules show promise and have clinical physiological similarities, but have not undergone extensive testing.

The systematic review of the predictive value of serum markers of inflammation and infection in children presenting with FNP included 27 studies reporting over 13 different markers derived from an initial screen of 375 studies. The studies included had similar methodological challenges as well as problems with reporting and analysis. Many failed to assess whether the marker had any supplementary value over and above the simple admission data collected by the clinicians at every encounter: age, malignancy, temperature, age-corrected vital statistics and blood count.

To interpret the information on serum markers in a clinically meaningful way, we had to allow for the marked heterogeneity of the results. The quantitative pooling and a qualitative summary of the results suggested that procalcitonin might be a better discriminatory marker than C-reactive protein (CRP) and that IL-6 had a very good ability to predict documented infection. Overall the findings were uncertain and unstable, and only small amounts of new data may alter them substantially. Data for the other markers were too sparse to reasonably be interpreted, although IL-8 had significant potential value.

These reviews have a wide range of rules for the prediction of poor outcomes during episodes of FNP in children and the use of a variety of individual serum markers to predict outcome. None of the rules found has yet been subjected to the extensive geographical and temporal discriminatory validity assessments that mark the highest quality CDR. Many potential difficulties with different outcomes, variable selection and model-building have been identified. The data on serum markers were extremely heterogeneous, and only tentative conclusions could be drawn.

The problems identified are inherent in the attempt to undertake meta-analyses of aggregate data. The limitations of the reporting in published studies mean we do not have access to the exact data distribution or the full range of univariable estimates of predictive power. These issues could be addressed by attempting to collect more detailed summary data from the authors of the original studies, but this would not allow cross-study validation of different rules or attempts at alternative rule-building. To meet these challenges and to maximise the value of the information already collected by these groups and in other cohorts of children with FNP, an IPD meta-analysis will enable us to develop and test new and existing prediction models. This will provide a firmer basis for stratified treatment trials in this common and occasionally fatal complication of therapy.

### Rationale for an individual participant data analysis

Individual patient data pooled analysis in therapeutic studies have been developed for two decades to improve the precision and reliability of answers to questions regarding treatment [24,25]. It has more recently been promoted for the synthesis of diagnostic data [26] and prognostic information [27] to improve the quality of answers to important prognostic questions [28] and matters of diagnostic accuracy [29]. These techniques have been applied to real-world clinical data sets [30,31], in which they have clarified existing understanding of particular prognostic variables and enhanced understanding of how different diagnostic tests can be used [32].

The key benefits of prognostic IPD analysis generally can be summarised as follows: (1) Analyses are not restricted to those of the published results or subgroups; (2) analytical techniques, inclusion criteria and outcome definitions can be standardised across studies; (3) larger numbers of data points allow more powerful statistical conclusions to be drawn, including checking modelling assumptions and accounting for missing data at the individual level; (4) IPD can model data more appropriately, such as by analysing continuous variables on continuous scales (unlike in many prognostic studies in which data are reported as categorical variables); (5) analysis can account for clustering (for example, of patients within studies) and correlated information (for example, multiple events per individual); (6) multivariate models can be created across different healthcare settings; (7) data can be reviewed for completeness and accuracy; and (8) the analysis can provide extensive internal cross-validation to guard against data-driven exaggerations of predictive power.

In the Predicting Infectious Complications of Neutropenic sepsis In Children with Cancer (PICNICC) study, the collection and analysis of IPD will provide specific benefits that overcome many of the problems found in the aggregate data meta-analysis. Many of the benefits of IPD analysis are technical, being related to the statistical methods underlying the meta-analysis and the building of predictive models. Although at first sight the failure to address the problems inherent in statistical interpretation may seem to be clinically irrelevant, it has clear and real clinical implications [33]. Other benefits are more obviously clinical; for example, the collection of the different data sets will enable us to clarify and harmonise the different outcomes collected.

One of the primary 'statistical' benefits will be the use of firmly prespecified potential predictor variables built upon the experience of the PICNICC Collaborative and the systematic reviews. This will guard against the development of purely data-driven analyses, which have a tendency to overestimate any predictive value [28].

In the reviews, we found the studies designed to build a CDR used a large number of variables (median = 13, range = 2 to 39) and had a small number of events (median = 36, range = 4 to 178) with 70% (12 of 16) studies having fewer than 10 events per variable under consideration and no study having more than 14 events per variable. These low event-per-variable ratios render predictive conclusions drawn from the studies unstable and estimates of predictive power overly optimistic [34]. IPD will allow us to consolidate the information and increase greatly the number of events studied from the same number of predictive variables.

The raw data will also allow a detailed analysis of the clustering of events (multiple episodes per patient) and variation at the level of the individual patient. This issue is significant when assessing the problems identified in the aggregate data reviews. Multiple episodes in individual patients were treated primarily as if they came from dissimilar individuals in the 20 CDR and 24 serum marker studies. Four papers explicitly described no adjustment [22,35-37], with 12 undertaking some attempt at assessment. Secondary analysis was performed to assess 'first included case' versus 'all episodes' and 'no significant differences' in three studies [22,38,39] and in nine others in which more advanced statistical modelling was used [6,21,40-46]. In 28 studies, the assessment was unclear.

The functional form of the data regarding *a priori *nonlinear fractional polynomial relationships can be assessed in detail. In no study assessed were clear attempts made to fit nonlinear forms to the data. This is unsurprising, as the development of practical techniques to undertake this effort is very recent [47].

Modern statistical developments in the handling of missing data may enhance the information already acquired. Again, very little information on the assessment and management of missing data was available from the reviews (five CDR studies [21,38,39,42,44] and two serum marker studies [48,49]). Very recent publications of studies in which simulation [50] and surveying practice [51] were used produced workable guidelines for the use of imputation techniques to maximise the value of the data collected. IPD will allow us not only to test existing rules and combine data derived from attempts to examine the rules but also, potentially, to develop a more robust rule for future use worldwide.

### Parent and/or caregiver involvement

The development of shared research initiatives involving patients, clinicians and researchers has been a notable change in the practice of clinical research over the past decade [52]. It remains surprising to many researchers, clinicians and patients when they learn that their views are often strikingly different from each others' [53]. A systematic review of studies of the process of research planning and priority setting undertaken by the James Lind Alliance [52] demonstrated that the involvement of patients and parents as well as other caregivers was extremely infrequent.

The PICNICC group has sought to involve parents early in the treatment process. Discussions of the nature of their engagement in the process have so far highlighted that the representatives involved have not wished to be actively involved in the process of reviewing, but to be included in discussions about the nature of, the adverse effects of FNP and that they have been willing to provide their own nonmedical expertise in advancing the project.

The discussion of the nature and extent of patient and caregiver involvement in the PICNICC group will continue as the project develops. Possible opportunities for further involvement include writing commentaries on the study for patients and their families, providing alterative views on ethical questions, making choices regarding risk thresholds and considering how uncertainty and imprecision should be managed.

## Methods

### Aims

#### Primary

A primary aim of the project is to undertake an IPD pooled analysis to quantify the risk of adverse clinical outcomes according to clinical variables in children and young people undergoing treatment for malignant disease who present with an episode of FNP; that is, to identify which variables are prognostic and which have the most independent prognostic importance. Another primary aim is to develop and validate a new risk prediction model containing multiple prognostic factors in combination.

#### Secondary

The secondary aim of this project is to develop and explore practical and methodological issues surrounding the use of pooled IPD analysis in the development of predictive models.

#### Inclusion and exclusion criteria

Studies will be considered for inclusion in the IPD meta-analysis if they are cohort studies of children and young people presenting with FNP and/or with either prospective or retrospective data collection, including RCT data; if they provide data for all 'essential' predictive variables in more than 50% of included episodes (see 'Core data set and variables' section); and if they provide details of two or more study-defined outcomes in more than 90% of individual episodes of FNP.

Studies will be excluded if they are case series (for example, studies of only 'Gram-negative bacteraemias') and if they did not record data on all 'essential' predictive variables or cannot provide sufficient outcome data.

Studies will be included if they focus on the collection of data from children and young people (between 0 and 24 years old). The purpose of the inclusion criterion of studies of young people up to the age of 24 years is to address a paucity of research on individuals in the 'young adult' age range [54]. Data from individual patients ages 25 years and older will be excluded from this analysis. The median age of inclusion in the 'children's' cohorts examined in our reviews was about 7 years old (ranging from 1 month to 23 years), and the 'adult' study from the Multinational Association for Supportive Care in Cancer group [55,56] has a median age of 52 years (range, 16 to 91 years old).

### Identification of potential studies

The initial identification of studies has been through extensive literature searches undertaken as part of the systematic reviews reported briefly in the Additional material at the end of the protocol (see Appendix 1 in Additional file 1 for a list of studies).

The following databases were searched by two independent reviewers to identify potential collaborators: MEDLINE, MEDLINE in-process and other nonindexed citations, Embase, Cumulative Index to Nursing and Allied Health Literature, *Cochrane Database of Systematic Reviews*, Database of Abstracts of Reviews of Effects, Health Technology Assessment Database, Cochrane Central Register of Controlled Trials, Thomson Reuters Conference Proceedings Citation Index-Science and Literatura Latinoamericana y del Caribe en Ciencias de la Salud. The reference lists of relevant systematic reviews and included articles were reviewed for further relevant studies. Published and unpublished studies were sought, and no language restrictions were applied. Non-English-language studies were translated into English. (See Appendix 2 in Additional file 2 for a sample search that we conducted.)

Further analysis of the initial literature searches will be undertaken to identify any published cohorts of FNP patients that may have been excluded from the reviews because a CDR or serum marker was not tested, yet could provide the information essential to being included in the IPD study. In addition to this, open calls for participation have been made via the International Society for Paediatric Oncology Supportive Care Group, the University of York Centre for Reviews and Dissemination website (http://www.york.ac.uk/inst/crd/projects/picnicc_patient.htm), presentations at relevant UK and international conferences, and via the Oncopedia web community of paediatric oncologists (https://www.cure4kids.org/ums/home/index.php?location=%2Fums%2Foncopedia%2F).

### Core data set and variables

This IPD meta-analysis will develop a risk stratification model to predict which children and young people have a low risk of adverse outcomes during an episode of FNP. The predictor variables and adverse outcomes sought have been based on our systematic reviews of aggregate data, in which exploratory analysis showed that age, malignant disease state, clinical assessment of circulatory and respiratory compromise, higher body temperatures and bone marrow suppression had explanatory value and reflected clinical experience of the paediatric oncologists.

The following predictor variables are divided into 'essential' and 'desirable' items and can be categorised as (1) patient-related, episode-related clinical variables and (2) patient-related, episode-related laboratory variables:

1. Age

2. Underlying tumour type

3. Marrow involvement and/or remission status

4. Chemotherapy type and time elapsed since last cycle

5. Presence of central venous line

6. Inpatient or outpatient at onset of episode

7. Maximum temperature

8. Antibiotic therapy used

9. Respiratory rate (or compromise)

10. Circulatory parameters (or compromise)

11. Severe mucositis

12. Global assessment of illness severity

13. Haemoglobin

14. Platelet count

15. White blood cell count

16. Neutrophil count

17. Monocyte count

18. CRP

19. Procalcitonin

20. IL-6

21. IL-8

The following are outcomes of primary interest from each episode:

1. Death

2. ICU admission

3. Need for moderate organ support (fluid bolus, oxygen)

4. Clinically documented infections

5. Microbiologically documented infections

Two or more of these outcome measures should be provided for more than 90% of episodes.

If available, we will also collect data on the following:

1. Duration of fever

2. Duration of admission

An example of the initial survey of data available from collaborators is provided in Appendix 3 in Additional file 3. An *a priori *mapping schema linking microbiological and clinical outcome variables into a unified description of 'severe' and 'nonsevere' infections has been developed to assist with unifying outcome definitions.

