### Plan of investigation

#### Method of analysis

The primary method of analysis for the PICNICC study will be the use of multivariable logistic regression modelling. There are a series of different analytical techniques that can be used to produce rules, including multivariable regression analysis, classification and regression tree (CART) models, discriminant analysis and neural networks. There is no clear evidence that one method is superior to any other [58], and, as multivariable logistic models have the widest clinical understanding and applicability, this method has been selected.

In the primary analysis, data used will be from the first recorded episode for each patient to predict an absence of adverse outcomes due to the individual episode (that is, death, intensive care requirement, medical complication, bacteraemia or other significant bacterial infection). Following the primary analysis, outcome data and predictor variables from subsequent episodes will be analysed to assess the independence or otherwise of these data, and this information will also be included using an appropriate model.

Prospective and retrospective cohorts will be considered separately in the initial analyses on the basis of the hypothesis that there will be a clinically important difference between the two types of studies. If no difference is found, then the data set will be examined as a whole. The prognostic importance of individual variables, both unadjusted and adjusted for other variables (the latter to summarise independent prognostic value), will be summarised for each study.

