### Model development

The model will initially incorporate the simplest predictor variables (malignant diagnosis, age, time since chemotherapy, and maximum recorded temperature) before standard additional variables (such as clinical assessments of compromise, inpatient or outpatient status, white blood cell counts or other haematological parameters) are added. Further specialist tests (for example, CRP and IL-6 levels) will be added. The type of antibiotic therapy used will always be incorporated into the model as a categorical variable. Potential sources of heterogeneity (for example, in effects of particular variables across studies) will be incorporated as random effects as appropriate. The models will be assessed for improvement in fit by using an information criterion (for example, Akaike's information criterion) with a *P*-value of < 0.15 used for inclusion. We will use a 15% rather than a 5% level, as we feel this is more conservative and will limit the chance of missing important covariates. At the stage of deciding our final model, however, we will check that the model's predictive accuracy (discriminatory ability) is improved by the inclusion of variables whose significance is between 5% and 15%. If predictive accuracy is not improved, then these variables will be removed.

This approach (of adding specialist tests only after considering the simpler tests) maximises the utility of a model by ensuring that, if extra tests with their additional costs are required, they will add considerable predictive power to existing simpler variables [61]. We will use bootstrapping and shrinkage to adjust for potential overoptimism (bias) in parametric estimates and trends.

Continuous candidate variables will be assessed using the best fitting functional form considering appropriate transformations or fractional polynomials (also assessed using an information criterion) as suggested by previous evidence. Missing data will be examined to define the nature of the 'missingness'. If they are missing at random, then multiple imputation techniques will be used to address these gaps utilising all the other available data [50,51]. The results of these analyses will be compared with a complete case analysis. We will conduct an analysis comparing the new model that we develop with other validated models, for example, that of Santolaya *et al. *[62]. This will provide an opportunity to test these CDRs against data from other geographical areas.

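### Circulatory or respiratory compromise is a predictor and need for a fluid bolus or oxygen is an outcome, but no prediction time or outcome start is set, so one event can be scored as both

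*Protocol article*

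**What the plan says.** **Predictors.** Under Core data set and variables, items 9 and 10 of the predictor list are "Respiratory rate (or compromise" and "Circulatory parameters (or compromise". The same section says that in the preparatory reviews "clinical assessment of circulatory and respiratory compromise, higher body temperatures and bone marrow suppression had explanatory value". Under Model development, the first stage uses diagnosis, age, time since chemotherapy and maximum temperature. Compromise enters at the second stage, among additional variables "such as clinical assessments of compromise, inpatient or outpatient status, white blood cell counts or other haematological parameters".

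**Outcomes.** The outcome list in Core data set and variables opens with "The following are outcomes of primary interest from each episode", and its third item is "Need for moderate organ support (fluid bolus, oxygen". Under Method of analysis, the primary analysis predicts the absence of a composite: "death, intensive care requirement, medical complication, bacteraemia or other significant bacterial infection".

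**Timing.** Background describes a risk prediction model as one that predicts a future outcome. The summary of the serum-marker review treats vital signs and blood counts as information gathered at admission. No section shown states when predictors 9 and 10 are measured, from when an outcome counts, or how support already in place is handled. Data format asks, ideally, for one row per episode.

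**The concern.** Oxygen and a fluid bolus are responses to respiratory and circulatory compromise. A child who arrives compromised and is treated straight away can score positive on predictor 9 or 10 and on outcome 3 for one and the same event. In such a child the model describes the present state and predicts nothing.

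Three results are exposed:

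- the ranking of variables by independent prognostic importance, which is a primary aim;
- the AUC and sensitivity planned under Assessing model performance;
- the cutoff, which is read from the same ROC curve.

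The performance of most clinical interest is in children who look stable when assessed, and it could be lower than the reported figure. Bootstrapping, shrinkage and leave-one-study-out validation do not help. They correct overfitting, and they reuse the same outcome definition.

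**Working it through.** The article gives no figure on this point, so there is nothing to reproduce. The check is a comparison of the text, followed by two illustrations.

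**1. Text.**

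| Element | What the article fixes | Time stated |
|---|---|---|
| Predictors 9 and 10 | rate or parameters, or compromise | none (admission is implied by the review summary) |
| Outcome 3 | need for fluid bolus or oxygen | the episode |
| Primary composite | includes medical complication | due to the episode |
| Data checks | implausible values, missing-data codes, outlier studies | no check that the outcome follows the predictors |

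Nothing in these rows stops one event from filling both sides of the model. The first-stage model has no compromise term, so the direct overlap begins at the second stage.

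**2. Illustration by arithmetic.** Only the 25% event rate has a source: the Abstract says about three-fourths of patients do not need aggressive treatment. The other inputs are assumptions. A share *p* of 1% to 6% of all children already have the outcome at time zero. Compromise is recorded in *c* = 80% to 95% of those, in 8% of children with later events and in 5% of the event-free.

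Probability of compromise given an event = [*p*·*c* + (0.25 − *p*)·0.08] / 0.25. The event-free odds are 0.05/0.95 = 0.0526.

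- Later events only: (0.08/0.92)/0.0526 gives an odds ratio of 1.65.
- *p* = 0.01, *c* = 0.80: (0.0080 + 0.0192)/0.25 = 0.1088, odds ratio 2.32.
- *p* = 0.06, *c* = 0.95: (0.0570 + 0.0152)/0.25 = 0.2888, odds ratio 7.72.

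Sensitivity, for a rule with 80% sensitivity for later events that flags every time-zero case = [*p* + (0.25 − *p*)·0.80] / 0.25.

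- *p* = 0.01: (0.010 + 0.192)/0.25 = 80.8%.
- *p* = 0.06: (0.060 + 0.152)/0.25 = 84.8%.

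If the rule flags only a share *c* of the time-zero cases, the first term becomes *p*·*c*:

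- *p* = 0.01, *c* = 0.80: (0.008 + 0.192)/0.25 = 80.0%, no change.
- *p* = 0.06, *c* = 0.95: (0.057 + 0.152)/0.25 = 83.6%.

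**3. Illustration by simulation.** Each scenario had 200,000 episodes. The later-event rate was 25% or 33%; the second value comes from the statement in Background that two-thirds or more of episodes may have no significant infection. One genuine score had an AUC of 0.65 or 0.70. Compromise was present in 5% to 15% and given no prognostic value for later events, and 50% to 90% of compromised children were supported at once. A logistic model with score and compromise was fitted twice.

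| | Support at presentation counted | Those episodes left out |
|---|---|---|
| Odds ratio for compromise | 4.4 to 54.1 | 0.86 to 1.09 |
| AUC, true 0.65 | 0.669 to 0.779 | about 0.65 |
| AUC, true 0.70 | 0.713 to 0.808 | about 0.70 |

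Between 5% and 29% of the counted events were events only because of support at presentation. The simulation shows the mechanism and its direction. Its odds ratios follow from the assumed treatment share and are not evidence of the size to expect here.

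**The case against.** A reader might infer that children who already have the outcome are in fact counted as predicted events, and that performance is therefore inflated. The documents do not support that. Neither the predictors nor outcome 3 carry a time, and immediate treatment at presentation is a reading of the lists. The intended order is also visible, since Background speaks of a future outcome and the review summary of admission data. What is missing is the operational cut-off. This stands, and the point is limited to what the text permits.

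A reader might also take outcome 3 to be part of the composite as a documented fact. Method of analysis does not name it. Its components resemble the review categories, where the item is serious medical complications, while outcome 3 is moderate support. Inclusion is the natural reading, because outcome 3 is listed as of primary interest, but it remains an assumption.

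Further limits stand:

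- Data sets that supply a rate or a measured parameter record a sign and not the treatment, so the overlap is partial.
- For a fixed rule that flags every time-zero case, the event rate in the low-risk group does not change.
- Removing already supported children from the analysis would change the target population, and the article also wants to define a very-high-risk group.
- The coding appendix is not shown and could hold timing rules. A condensed article commonly leaves such detail elsewhere.

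The last objection does not dispose of the point. The article itself places overlapping constructs in its predictor list and its list of primary-interest outcomes, and the resulting choice alters reported results.

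**Conclusion.** The point holds in limited form. Predictors 9 and 10 overlap with outcome 3, and the visible text sets neither a prediction time nor an earliest time for counting an outcome. From the second model stage on, one event can enter as predictor and outcome. This can inflate the odds ratio for compromise, the AUC and the sensitivity, and the planned internal validation cannot remove it.

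The size is unknown. Under the stated assumptions sensitivity would read 80.8% to 84.8% in place of 80%, and less if some time-zero cases are not flagged. The effect on the odds ratio is larger, 2.32 to 7.72 against 1.65. These are not trial figures. The effect on the primary analysis rests on outcome 3 belonging to the medical complication component, and on some children being supported when the predictors are recorded. The change should be made, with medium confidence.

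**What to change.** 1. State the prediction time and take predictors only up to it.
2. State whether outcome 3 belongs to the medical complication component of the composite.
3. Where timing is available, count only outcomes that start after the prediction time, and describe separately the episodes that already meet the outcome.
4. For all data sets, and in particular those without timing, refit any model containing compromise with outcome 3 left out of the composite. Report odds ratios, AUC and sensitivity both ways.

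**Cost.** Step 3 needs a query to the data providers. Data checking already provides for queries to each study, and Status of the project says no analyses have been done. However, 23 data sets have already been collected, and retrospective ones among them may be unable to answer. Step 4 needs no new data: it costs one extra model, fewer events and possibly a less favourable AUC.
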